### Participant timeline {13}

During BL, patients will undergo a short-structured interview using the MINI-DIPS (Mini Diagnostic Interview for Mental Disorders) to screen for mental disorders. The chapter on MDD from the Diagnostic Interview for Mental Disorders (DIPS) will be used to characterize the symptoms of depression further. Demographic information, such as sex, age, education, and employment, will also be recorded.

Routine blood work, including inflammation markers, lipid markers, and vitamin status, will be performed at baseline and on day 49 (± 3). Medication intake, symptom severity (assessed using MADRS and HDRS-24), and DOTES will be assessed weekly. The BDI-II will be administered biweekly according to the instructions provided (Table 2).

**Table 2 Tab2:** Overview of examinations during the BDNF trial

	STUDY PERIOD					
TIMEPOINT	Screening (day 0)	Baseline (day 0-7)	Weekly examinations	Biweekly-examinations	Follow Up (day 49 +/- 3)	Follow Up by phone (day 70 +/-3)
ENROLMENT:						
Eligibility screen	X					
Informed consent	X					
Allocation		X				
ASSESSMENTS:						
MINI-DIPS (+ MD-DIPS)		X				
Demographics (sex, age, education, employment, social network, marital status, living situation)		X				
Routine blood work (HDL, LDL, Triglyceride, cholesterol, differential blood count, HbA1c (only BL), CRP, 25-OH-Vitamin D3, Vitamin B12, folate, cortisol, TSH, Insulin, Na, K, Ca, Cl, CK, eGFR, Kreatinin, GOT, GPT, gammaGT)		X			X	
BDNF blood withdrawal		X				
Current medication and side effects		X	X		X	X
Psychotherapy		X	X		X	X
Other treatment modalities		X	X		X	X
BDI-II		X		X	X	X
MADRS		X	X		X	X
HDRS-24		X	X		X	X
DOTES		X	X		X	X

### Sample size {14}

To calculate the required sample size for the study, assumptions regarding the prevalence for biomarker-positive patients, as well as the rates for the co-primary endpoints in both treatment groups, must be established.

#### 2nd co-primary endpoint (AE rate)

In a meta-analysis conducted by [21], which examined the efficacy of SSRIs and the incidence of AEs based on placebo-controlled studies, the median AE rate was 0.8 in the treatment group. In this trial, it is assumed that knowing the marker status will result in a reduced use of antidepressants, leading to fewer AEs during pharmacotherapy. Conservatively, it is assumed that the AE rate will be half in the biomarker-negative group compared to the rate in patients treated with antidepressants (AE rate in antidepressant-treated patients: 0.8, AE rate in patients not treated with antidepressants: 0.4). Therefore, it is assumed that the AE rate in the marker group is 0.6, calculated as the mean of the expected AE rates stated. Since all MDD patients in the TAU group receive antidepressant treatment, an AE rate of 0.8 is assumed. A sample size of 218 achieves 90% power to detect a rate difference of − 0.20 (marker − TAU group) for the assumed AE rates, with a one-sided type I error of 2.5%.

To demonstrate the value of knowing the marker status for both co-primary endpoints with sufficient robustness, the final sample size was determined based on the 1st primary endpoint, which requires a larger sample size (*n* = 222 vs. *n* = 218). To compensate for potential treatment effect reduction due to study dropouts, the sample size is increased by 15% to ensure a conservative sample determination (*n* = 256). Sample size calculation was performed with nQuery 9.3.

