Over the past few decades, there has been a significant advancement in the field of precision medicine. Although there is promising potential in the form of numerous biomarkers that require verification or falsification, precision psychiatry has yet to catch up [10, 11]. Precision psychiatry aims to integrate biological and environmental data to customize treatments [11]. In this context, the brain-derived neurotrophic factor (BDNF) plays a crucial role concerning antidepressant treatment for MDD. It is implicated in the pathophysiology of MDD as well as the mechanism of action of antidepressants [12–15]. BDNF exon IV has been extensively studied. It acts in regulating its expression through DNA methylation and histone modifications. It contains promoter elements and controls the production of activity-dependent BDNF [16]. We have consistently demonstrated that the DNA methylation of a specific CpG site within the promoter region of exon IV of the BDNF gene is crucial for the effectiveness of current monoaminergic antidepressant treatments, such as selective serotonin reuptake inhibitors (SSRIs), serotonin-norepinephrine reuptake inhibitors (SNRIs), and others [17–19].

Following an initial study conducted by Tadic et al. [17], in which a potential marker was identified in 44 depressed patients, we were able to replicate and validate this finding in a larger cohort of 199 severely depressed patients from the Early Medication Change study (EMC) [18]. In the EMC study, it was observed that patients exhibiting methylation at the CpG site -87 had an almost threefold higher likelihood of achieving remission than those with an unmethylated CpG site. These results were further supported by in vitro experiments, where the effective signaling of BDNF, stimulated by antidepressant incubation, was observed exclusively in constructs with a methylated BDNF exon IV promoter [17, 19]. Wang et al. [20] reported similar findings in a large sample of Chinese patients. However, there is a lack of prospective data regarding the potential of this marker to impact therapeutic decisions.

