**Inclusion criteria**	
Age	≥ 18– ≤ 70
Sex	Male, female, or diverse
Major depressive episode according to ICD-10 (F32.2–3, F33.2–3)	Single or recurrent episodes, as confirmed by the DIPS
Symptom severity	Severe (MADRS ≥ 34)
Modification in the therapeutic regimen is being considered	e.g., change of AD or change to neuromodulatory therapy
First MDD episode < 50 years	
Capacity for consent	
Written informed consent	

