### Relevant concomitant care permitted or prohibited during the trial {11d}

This intervention occurs within a real-world setting, and as such, no concomitant care or interventions are excluded.

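### The AE power rests on every TAU patient receiving an antidepressant, but eligibility and open care do not ensure it; any shortfall dilutes the planned difference

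*Protocol article*

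**What the plan says.** In Sample size {14}, 2nd co-primary endpoint, the AE effect is built wholly from antidepressant use. Treated patients are given a rate of 0.8; the other input is "AE rate in patients not treated with antidepressants: 0.4". For the marker arm, "it is assumed that the AE rate in the marker group is 0.6, calculated as the mean of the expected AE rates stated". For the TAU arm the text is categorical: "Since all MDD patients in the TAU group receive antidepressant treatment, an AE rate of 0.8 is assumed". From these inputs, "A sample size of 218 achieves 90% power to detect a rate difference of" −0.20, tested one-sided at 2.5%.

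Other sections describe a wider range of care:

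- Table 1 requires that a modification of the regimen is under consideration, and illustrates this with "e.g., change of AD or change to neuromodulatory therapy".
- Explanation for the choice of comparators {6b} leaves TAU treatment to guidelines, the physician's experience and ward practice. Intervention description {11a} sets no treatment protocol.
- Section {11d} states that "no concomitant care or interventions are excluded".
- Adverse event reporting {22} describes a scale that covers ECT, rTMS and intranasal esketamine as well as drugs.
- The secondary outcomes in {20a} include the rate of antidepressant prescription and the rate of other treatment options.

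**The concern.** The sample size section treats universal antidepressant use in TAU as a fact. No other section makes it true, and one of the two examples in the entry criterion points the other way. The premise matters because it is the only source of the TAU rate of 0.8, and so of the difference that the second co-primary endpoint is powered to detect.

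The trial succeeds only if both co-primary criteria are met. The protocol also relies on the AE reduction when it defends the 20% non-inferiority margin. If some patients receive the same non-antidepressant treatment in either arm, they contribute no AE difference and the contrast between arms shrinks.

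A related point is interpretation. The introduction says that "there is a lack of prospective data regarding the potential of this marker to impact therapeutic decisions". Table 2 lists current medication and other treatment modalities at baseline, but not the treatment intended next. Without that item it is hard to examine how far dilution explains a small AE difference.

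**Working it through.** **Inputs from the protocol article.** AE rates 0.8 (TAU), 0.6 (marker) and 0.4 (no antidepressant); one-sided 2.5%; 90% power; 1:1 allocation; 222 patients (111 per arm) before the 15% increase to 256.

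**Reproducing the plan.** With the pooled-variance formula for two proportions, n per arm = [1.96·√(2·p̄(1−p̄)) + 1.2816·√(p₁(1−p₁)+p₂(1−p₂))]² / d². With p₁ = 0.6, p₂ = 0.8, p̄ = 0.7 and d = 0.2:

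- 1.96 × √0.42 = 1.270 and 1.2816 × √0.40 = 0.811; the sum is 2.081.
- 2.081² / 0.04 ≈ 108.2, so 109 per arm and 218 in total. This matches the plan.

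The non-inferiority figure also reproduces: 0.42 × (1.96 + 1.2816)² / 0.04 ≈ 110.3, so 111 per arm and 222 in total. Finally, 222 × 1.15 = 255.3, rounded up to 256. The arithmetic is sound, so the question is only the input of 0.8.

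**Sensitivity.** Assume that a share q of each arm receives the same non-antidepressant treatment whatever the marker shows, with AE rate r, and that everyone else follows the plan's rates:

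- TAU rate = 0.8(1−q) + rq
- Marker rate = 0.6(1−q) + rq
- Difference (TAU − marker) = 0.20(1−q)

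The documents give neither q nor r for such patients. r = 0.4 is the plan's rate without antidepressants. r = 0.8 allows for other treatments causing as many AEs, since the scale counts AEs of ECT, rTMS and esketamine too.

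Power = Φ{[d − 1.96·√(2p̄(1−p̄)/n)] / √([p₁(1−p₁)+p₂(1−p₂)]/n)}, with n per arm.

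Worked case, q = 20%, r = 0.4, n = 111: the rates are 0.72 and 0.56, d = 0.16 and p̄ = 0.64. The null standard error is √(2 × 0.2304/111) = 0.0644 and the alternative one is √(0.448/111) = 0.0635. Then (0.16 − 1.96 × 0.0644)/0.0635 ≈ 0.53, and power is 70.2%.

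| q | r | TAU vs marker | Power, 222 | Power, 256 | Total N for 90% |
|---|---|---|---|---|---|
| 0 | – | 0.80 vs 0.60 | 90.7% | 94.2% | 218 |
| 5% | 0.4 | 0.78 vs 0.59 | 86.7% | 91.0% | 248 |
| 5% | 0.8 | 0.80 vs 0.61 | 87.9% | 92.0% | 238 |
| 10% | 0.4 | 0.76 vs 0.58 | 81.8% | 86.9% | 284 |
| 10% | 0.8 | 0.80 vs 0.62 | 84.5% | 89.2% | 264 |
| 20% | 0.4 | 0.72 vs 0.56 | 70.2% | 76.3% | 376 |
| 20% | 0.8 | 0.80 vs 0.64 | 76.0% | 81.7% | 328 |
| 30% | 0.4 | 0.68 vs 0.54 | 57.2% | 63.3% | 506 |
| 30% | 0.8 | 0.80 vs 0.66 | 65.3% | 71.6% | 420 |

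The loss arises at either value of r. The full 256 keeps 90% power at q = 5% but not at 10%, and the increase to 256 is already meant to offset dropout.

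**The case against.** A reader might infer that the eligibility rule admits patients whose switch to neuromodulation is already settled, so that part of the sample cannot show the effect. The documents do not support that:

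- Table 1 speaks only of a change under consideration and lists neuromodulation as an example. An open decision is where a marker can act: a result might steer such a patient towards or away from an antidepressant.
- No section says that neuromodulation replaces an antidepressant. As no concomitant care is excluded, a TAU patient may receive both, and the premise can then hold for that patient.
- The premise has some support. The introduction says that guidelines recommend starting with an antidepressant and that stimulation therapies usually come later.

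Nor can one say that the marker's influence on treatment is unanswerable. The arms are randomised and stratified by methylation status, so comparing them on antidepressant prescription, therapy changes and other treatments estimates that influence without any record of prior intention. Those comparisons also help in reading a null AE result.

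The non-inferiority calculation is unaffected, because it already assumes equal remission of 0.30 in both arms. The Discussion acknowledges that free treatment choice complicates attribution. The eCRF, which is not shown, may already record the intended treatment.

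All of this stands and limits the point. It does not make universal antidepressant use in TAU something that the protocol ensures, and the planned AE difference still depends on it.

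**Conclusion.** The point holds as a weakness in a planning assumption. Table 1 and the open-care sections do not ensure the premise behind the TAU rate of 0.8, and the passages must be reconciled. Any share of patients treated alike without antidepressants in both arms shrinks the AE difference in proportion, and 90% power at 222 has almost no slack: 90.7% at q = 0, and 86.7–87.9% at q = 5%.

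The size is conditional. It rests on an assumed q, on r between 0.4 and 0.8, on the plan's own rates in everyone else, and on an unstratified normal approximation, whereas the planned analysis is stratified. If nearly all TAU patients do receive an antidepressant, alone or with other treatment, the loss is small. The effect remains testable, and this point takes no position on which treatment patients should receive.

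**What to change.** 1. In Sample size {14}, replace the statement about all TAU patients with an assumed share receiving antidepressants. Derive both arms' AE rates from it and restate the AE power over a range of q, keeping enrolment at 256. Align the wording with Table 1 and {11d}.
2. Unless the eCRF already holds it, add one mandatory field, completed before randomisation in both arms: the treating physician's intended next treatment (monoaminergic antidepressant, neuromodulation, esketamine, other).
3. Pre-specify a supportive, non-confirmatory analysis of both co-primary endpoints in patients for whom a monoaminergic antidepressant was intended. Also report secondary endpoint (b) as change from the intended treatment.

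**Cost.** One eCRF field, a less favourable stated power, and an amendment to {20b}, which currently plans no subgroup analyses. No patients or visits are added. Trial status says that recruitment has not begun, so the field can still cover every patient; intention before allocation cannot be reliably reconstructed later.

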### Recruitment {15}

Patient recruitment occurs within the larger multicenter cohort study “P4D—Personalized, Predictive, Precise & Preventive Medicine for Major Depression” (for additional information, refer to the German Clinical Trial Register (DRKS) ID: DRKS00032215). Briefly, individuals diagnosed with depression will undergo screening upon admission to a psychiatric ward at any of the five participating university hospitals.

## Assignment of interventions: allocation

### Sequence generation {16a}

The marker status information will be transmitted to the respective study sites’ electronic data management system based on the randomization of the study participants. Patients randomized into the TAU group will not have access to their marker status. Randomization occurs after analyzing the marker status using subject data, which helps to guide the stratification process. The randomization list, incorporating sex, methylation status, and center as stratification characteristics, is created by the Institute of Biometry at MHH and implemented by the data management team in the eCRF. The eCRF is facilitated using the electronic data capture system MARVIN (XClinical). To maintain the blinding of raters, the marker status will be made available to the platform members via the electronic data management system once the diagnostic study is completed.

### Concealment mechanism {16b}

Allocation concealment will be guaranteed, as the randomization code will not be generated until the patient has completed all essential baseline measurements within this diagnostic trial.

### Implementation {16c}

The study physician at each site will receive notification once the randomization for a patient is finalized. The allocation will be disclosed to the patient and the treating physician, but it will remain concealed from the rater who is blinded to the study group.

## Assignment of interventions: blinding

### Who will be blinded {17a}

Assessments will be performed by psychiatrists who are not otherwise participating in the study to maintain blindness to the study group. Patients will be advised before each rating session not to disclose whether they belong to the marker group or not.

### Procedure for unblinding if needed {17b}

Given that our trial involves a marker rather than a drug, there will be no need for emergency unblinding.

## Data collection and management

### Plans for assessment and collection of outcomes {18a}

Patient data will be pseudonymized and recorded in an electronic case report form (eCRF). Patients will either receive a tablet (iPad) for self-administration of self-report questionnaires (e.g., Beck’s Depression Inventory II; BDI-II), or the rater will conduct the assessment and enter the corresponding responses directly into the eCRF (e.g., MADRS). Third-party ratings (MADRS, HDRS-24) will also be collected via eCRF. The administration of the scales can be conducted using a tablet or pen and paper, as per the rater’s preference with subsequent data transfer.

### Plans to promote participant retention and complete follow-up {18b}

Patients will be in the psychiatric ward for a minimum of 49 days. Participation in this diagnostic trial will only impact treatment if the marker status is known. However, the decision on the chosen treatment strategy will ultimately rest with the treating physician and the patient. The study protocol does not provide guidance on the treatment.

In the event of withdrawal from the study, a brief retention follow-up, including MADRS, HDRS-24, DOTES, and current treatment modalities, will be conducted. To ensure data quality for the co-primary endpoints, a phone follow-up will occur on day 49 ± 3, collecting MADRS, HDRS-24, DOTES, and information on current treatment modalities.

### Data management {19}

Clinical data is recorded using the electronic data capture system Marvin (XClinical), which complies with European data protection legislation, specifically the General Data Protection Regulation (GDPR; Regulation (EU) 2016/679). The collected data will be transferred to the P4D Cloud hosted by Leibniz Universität Hannover (LUH). Access to this data is restricted solely to members of the P4D consortium. Since the uploaded data is pseudonymized, de-pseudonymization is not feasible, except at the site where the data is collected. Any distribution of data and rights for analysis and publication requires the approval of the steering committee.

### Confidentiality {27}

Personal data will be handled in compliance with the GDPR. Access to the data will be limited to study investigators and authorized personnel, controlled by appropriate authentication methods.

### Plans for collection, laboratory evaluation, and storage of biological specimens for genetic or molecular analysis in this trial/future use {33}

After obtaining the signed informed consent documentation, patients will undergo assessments following the study protocol, and EDTA whole-blood samples will be immediately sent to Fraunhofer ITEM (Hannover, Germany) for methylation analysis using nanopore sequencing (Oxford Nanopore Technologies plc). The assay will be used to measure reliably and reproducibly the DNA methylation at the CpG -87 locus. The measurements can be completed within days providing timely results for clinical decision making. Fraunhofer ITEM will conduct the establishment, standardization, and validation of the assay following international standards and necessary quality assurance systems before the start of the diagnostic study. After analysis of the marker, the remaining portion of the samples, blood as well as DNA, will be discarded.

## Statistical methods

### Statistical methods for primary and secondary outcomes {20a}

#### Primary outcome

Two co-primary endpoints have been established, which can be translated into the following pairs of statistical hypotheses:

1st Co-primary endpoint:H0: Δ (remission rate marker group − remission rate TAU group) ≤ − 0.2H1: Δ (remission rate marker group − remission rate TAU group) > − 0.22nd Co-primary endpoint:H0: Δ (AE rate marker group − AE rate TAU group) ≥ 0H1: Δ (AE rate marker group − AE rate TAU group) < 0

The primary analysis will be conducted on the intention-to-treat (ITT) population, which includes all patients evaluated in the group to which they were randomly assigned. In cases of missing data, imputation will be performed by considering them as “Treatment Failures” for the “Response Rate” endpoint or as having “Had at least one adverse event” for the “Adverse Events” endpoint. The primary effect estimator for both outcomes will be the Mantel–Haenszel estimator for rate differences, explicitly calculating the difference between the marker and the TAU group, while considering methylation status, treatment center, and sex as strata. The *p*-value and confidence intervals will be calculated using the Cochran-Mantel–Haenszel test procedure. If the lower bound of the 95% confidence interval is above − 0.2, it indicates that the non-inferiority of the marker group compared to the TAU group in terms of remission rate can be demonstrated.

For the 2nd co-primary endpoint, the study aims to demonstrate the superiority of the marker group over the TAU group regarding the rate of adverse events. This second co-primary endpoint is met if the upper limit of the 95% confidence interval is less than 0.

To consider the study successful, both criteria must be met. First, non-inferiority for the 1st co-primary endpoint needs to be demonstrated, which means that the marker group should not be significantly worse than the TAU group in terms of remission rate, with the lower bound of the 95% confidence interval above -0.2. Second, superiority for the second co-primary endpoint should be demonstrated, indicating that the marker group has a significantly lower rate of AE compared to the TAU group, with the upper bound of the 95% confidence interval below 0.

#### Secondary outcome

The study’s secondary endpoints are analyzed descriptively, and the evaluations follow the same principles as the primary analyses. These secondary endpoints provide additional insights into various aspects related to the study. The critical secondary endpoints include the following: (a) rate of description of AD: this assesses the frequency at which AD is prescribed and described in the study population; (b) changes in therapy during the study duration: this evaluates any modifications or adjustments made to the treatment regimens of the patients throughout the study; (c) rate of specific psychotherapeutic treatment; (d) rate of other treatment options; (e) rate of and reasons for leaving the study early; (f) expectations and attitudes regarding AD treatment and use of biomarkers in participating patients and physicians: this explores the beliefs, opinions, and attitudes of both patients and physicians towards AD treatment and the use of biomarkers in the context of depression; (g) doctor-patient relationship.

#### Data analysis plan

The analyses of the primary and secondary endpoints are described in the study protocol (see **“**Statistical methods for primary and secondary outcomes {20a}**” **section).

